### Safety and adherence considerations

Participant burden of the intervention and measures was assessed by interviews and feedback from patients who participated in previous pilot trail. Complaints and adverse events will be recorded during the intervention period. If patients have serious complications during the intervention, the participants will be asked to discontinue the trial, and the doctor will administer appropriate treatment.

The intervention content of this study was based on the guideline of the American College of Sports Medicine and Institute of Medicine, and measures will be conducted in hospital by specialist doctors and trainers. The dose of vitamin D used in the present study is expected to significantly increase serum 25(OH)D concentrations and decrease glucose levels in T2DM patients [33] and is lower than the tolerable upper dose (2000 IU/day) for Chinese [34]. During the screening, baseline, intervention, and follow-up, any medical conditions or abnormalities detected will be promptly discussed with the participant by a qualified medical practitioner involved in the study. Participants are allowed to be treated, referred, or advised to visit their practitioner during the intervention. All participants will be informed of their screening blood test results after they have completed their participation in the study.

The double data entry is performed in the study. There is no special Data Monitoring Committee, as the Xi’an Jiaotong University Human Research Ethics Committee, which is independent of the trial sponsor and investigator to ensure recommendations are as objective as possible and unaffected by conflicts of interest, undertake this analysis per year. The data used in this study are not publicly available due to ethical reasons; the corresponding author can provide further information on these data upon reasonable request.

The researcher committee will evaluate and improve the protocol through email or online regular meeting. The research ethics committee of the university will be also notified whenever needed.

### Statistical analyses

Based on the relative studies on vitamin D intervention with IR [15], the sample size required for each group was estimated to be 12 with a power of 85%, and an effect size of 0.26 was assumed. Therefore, 48 T2DM patients are required. To account for 20% loss-to-follow-up, a total of 60 T2DM patients will be recruited. Power calculations will be performed using G*Power software version 3.1.9.2 [35].

Descriptive statistics will be calculated using mean (standard deviation) for continuous variables and *n* (%) for categorical variables. Differences will be compared using one-way analysis of variance (ANOVA) for continuous variables and chi-squared tests for categorical variables. Repeated measures ANOVA will be used to test the effect of vitamin D and exercise combined intervention on glucose and lipid metabolism, with adjustment for baseline levels of outcomes. A post hoc test with Bonferroni correction will be used to identify significant differences among the mean values when a significant main effect or interaction is identified. Finally, in the event of possible losses or dropouts, a statistical analysis will be performed by protocol and intention to treat. Data will be entered and cleaned using EpiData version 3.0 and managed and analyzed using the Statistical Package for the Social Sciences. Statistical significance will be set at *P* < 0.05.

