### Randomization

All patients who give consent for participation and who fulfill the inclusion criteria will be randomized. An investigator who is independent of this study will randomly divide the subjects into four groups according to a computer-generated random allocation table stratified by age and sex. The treatment allocation code will be placed in an opaque envelope labeled with a sequential number. Group allocation was unknown to participants, investigators, and data collectors. The randomization code was broken after the last participant finished the study. The four groups are as follows: the placebo control group (CG), vitamin D supplementation group (VG), endurance exercise group (EG), and vitamin D supplementation combined endurance exercise group (VEG). All patients will be instructed not to change their levels of general physical activity and dietary habits during the intervention period. Their dietary changes will be recorded monthly as well.

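### Bonferroni for the post hoc comparisons is valid, but a step-down rule such as Holm holds the same 5% familywise error and is never less powerful

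*Protocol article*

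**What the plan says.** The Protocol article, Statistical analyses, plans a repeated measures ANOVA adjusted for baseline and then fixes the follow-up rule: "A post hoc test with Bonferroni correction will be used to identify significant differences among the mean values". The post hoc tests are run only "when a significant main effect or interaction is identified". The threshold is given as "Statistical significance will be set at *P* < 0.05". No simultaneous confidence intervals are planned.

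The section does not say how many comparisons the correction covers, or at which visit. The Randomization section says that an independent investigator "will randomly divide the subjects into four groups": CG, VG, EG and VEG. Four groups make six pairs at one visit. That number is inferred and does not stand in the plan.

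On size, the same section states "an effect size of 0.26 was assumed", "Therefore, 48 T2DM patients are required" and "To account for 20% loss-to-follow-up, a total of 60 T2DM patients will be recruited". It gives no power for any pairwise comparison.

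**The concern.** The aims in the Introduction are the effect of vitamin D and the joint effect of vitamin D with exercise. Pairwise contrasts such as VG-CG and VEG-EG bear directly on both. With 12 completers per arm they have little power, so the choice of correction matters more here than in a large trial.

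Bonferroni compares every P value in a family of k with 0.05/k, even after some hypotheses have been rejected. Holm relaxes the divisor after each rejection. It therefore rejects everything that Bonferroni rejects and sometimes more, under the same 5% bound and with no added assumption. This is true for any family of two or more comparisons. At stake is some power on the contrasts of interest; the validity of the plan is not in question.

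**Working it through.** **1. The plan's own figure.** Inputs from Statistical analyses: effect size 0.26, 12 per group, N = 48, power 85%, alpha 0.05, 20% loss. Assumptions, because the section does not state them: the effect size is Cohen's f, the test is the group-by-time interaction, there are m = 2 measurements, and their correlation is ρ = 0.5.

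- λ = f² × N × m/(1 − ρ) = 0.0676 × 48 × 2/0.5 = 12.98, with 3 and 44 degrees of freedom.
- Power = 83.6%. With ρ = 0.52 it is 85.2%. So 85% at 48 is reproduced closely.
- 48/(1 − 0.20) = 60, as stated.

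This calculation concerns the overall effect. It contains no post hoc test, so the choice between Bonferroni and Holm does not alter it.

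**2. The thresholds, if the family is six pairs.** P values are ordered from smallest to largest.

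| Rule | Divisors of 0.05 |
|---|---|
| Bonferroni | 6, 6, 6, 6, 6, 6 (0.0083 each) |
| Holm | 6, 5, 4, 3, 2, 1 |
| Ordinary Shaffer | 6, 3, 3, 3, 2, 1 |

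Shaffer's second divisor is 3 because, once one pair differs, the four means can only split as 3+1 (three true pairwise nulls), 2+2 (two), 2+1+1 (one) or all different (none). Both step-down rules start at 0.05/6, as Bonferroni does. So the chance of rejecting at least one pair is the same under all three.

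**3. Power for one illustrative pattern.** Simulation of 100,000 trials, 12 per arm, two-sided pooled-variance t tests on 44 df, means 0/0.8/0.8/1.6 SD for CG/VG/EG/VEG. The means are assumptions and are not taken from the document.

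| Rule | Power, VG-CG |
|---|---|
| Bonferroni | 22.6% |
| Holm | 27.0% |
| Shaffer 6, 3, 3, 3, 2, 1 | 30.9% |

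VEG-EG is practically the same, since its true difference is also 0.8 SD. Holm gains 27.0 − 22.6 = 4.4 points and Shaffer 30.9 − 22.6 = 8.3 points.

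**4. Other patterns.** Simulation of 200,000 trials each, behind a significant four-group F test; average power per truly different pair.

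| Means (SD) | Bonferroni | Holm | Gain |
|---|---|---|---|
| 0, 0, 0, 1 | 38.4% | 40.9% | 2.5 |
| 0, 0.5, 0.5, 1 | 13.3% | 14.4% | 1.1 |
| 0, 0.5, 0.5, 1.5 | 34.5% | 37.3% | 2.8 |
| 0, 0, 1, 1 | 38.6% | 42.5% | 3.9 |

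In the first pattern the chance of at least one rejection is 61.7% with either rule.

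**5. Familywise error.**

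- All means equal: Bonferroni 4.0% without a gate and 3.8% behind the four-group F test.
- Three equal means and one 3 SD apart: Bonferroni 2.2%, Holm 4.4%.
- Largest value for the step-down rules over the patterns run: 4.9%, at means 0/0/3/3.
- Unadjusted pairwise tests after a significant F: 11.3% with three equal means and one 1 SD apart. The gate alone is therefore not enough, and some correction is needed.

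**6. The stated gate and divisors 3, 3, 3, 3, 2, 1.** Starting at 0.05/3 is justified only if the gate has already shown that the four group means differ at the analysed visit. The plan opens the gate on any significant main effect or interaction, and there are three assessment times. A time effect alone can open it while all four groups are equal, and then all six nulls are true. With the gate opened that way, these divisors give a familywise error of about 7.5%, against 4.0% for Bonferroni.

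**The case against.** The best case for leaving the plan alone is that Bonferroni is valid, standard and simple, and that nothing in the article contradicts its use. It supplies matching simultaneous confidence intervals, which step-down rules do not. Holm's gain is a few points per pair, it adds nothing to the chance of finding at least one difference, and the stated sample size does not depend on it. The means used above are assumed, and the family could be a few planned contrasts or pairs at several visits.

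All of that stands, and it limits the point to an optional improvement. It does not remove the point. Holm's advantage over Bonferroni needs no particular family size, and the section decides by P value without planning simultaneous intervals.

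A reader might infer three stronger things that the article does not support:

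- **That the gate already excludes equality of all groups, so 0.05/3 is safe from the first step.** It is not safe with this gate (step 6 of the working).
- **That the plan pays twice, for the gate and for the divisor.** In the 0/0.8/0.8/1.6 pattern, Bonferroni power for VG-CG is 22.6% with or without a four-group F gate, so the gate costs next to nothing.
- **That the plan fixes six comparisons at 0.0083 each.** It gives no number.

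**Conclusion.** The point holds as a cheap efficiency gain. Bonferroni controls the error rate, but Holm does so at the same 5% and is never less powerful. For all six pairs at one visit, 12 completers per arm and the illustrative 0/0.8/0.8/1.6 SD pattern, power for VG-CG or VEG-EG is about 23% with Bonferroni, 27% with Holm and 31% with ordinary Shaffer. In the other patterns examined Holm's average gain is about 1 to 4 points.

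These sizes rest on the inferred family of six, equal arms, a common variance and assumed means. The ranking of Holm over Bonferroni rests on none of them. The Shaffer divisors apply only to all six pairs of four means. Even with the better rule these contrasts remain weakly powered, so the change does not make up for the small arms.

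**What to change.** In Statistical analyses, replace the Bonferroni correction with a Holm step-down correction and report adjusted P values. State which comparisons form the family. If that is all six pairs of the four groups at one visit, Shaffer divisors 6, 3, 3, 3, 2, 1 may be named instead. Do not adopt divisors 3, 3, 3, 3, 2, 1 with the gate as written.

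To apply it, sort the unadjusted P values, multiply each by its divisor, carry forward the running maximum and cap at 1.

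The cost is one phrase in the plan and a spreadsheet adjustment of the SPSS P values. The downside is that there are no matching simultaneous confidence intervals. Unadjusted 95% intervals would be shown and labelled as such, and they can disagree with the adjusted P values. The change should be made before the randomization code is broken. No change to the sample size is needed.

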## Discussion

To the best of our knowledge, this is the first study to conduct a randomized trial to clearly determine the independent and combined effects of vitamin D supplementation and endurance exercise trial on IR in Chinese T2DM patients as measured by OGTT. The findings from the proposed study will not only provide new evidences that vitamin D supplementation plays an important role in reducing IR but also develops a simple and efficient method to improve IR and associated metabolic diseases for T2DM patients.

The number of people with T2DM worldwide has increased rapidly. It is estimated to reach over 700 million in 2045 including more than 120 million people with T2DM from China [36], which can lead to major social, health, and economic challenges. IR is not only considered an important pathological and physiological basis for the development of T2DM but also a major contributor to other complications, which would lead to atherosclerosis, myocardial infarction, stroke, and even death [37]. Hence, the effective and innovative methods of preventing and improving IR for T2DM population are urgently required.

Beyond its traditional role in maintaining bone health, higher serum vitamin D levels have also been found to be associated with low risk of developing T2DM and other metabolic diseases considering its potential effects on IR [3, 38, 39]. However, to date, the results of several studies conducted are inconsistent [8–13]. Moreover, considering the ethnic differences in insulin metabolism [40] and that studies on vitamin D supplementation on IR in T2DM patients have mainly focused on non-Asian populations, it is significantly important to investigate the effects of vitamin D on IR in Asians.

In addition to promoting GLUT-4 translocation and glucose uptake in skeletal muscle cells [21, 22], exercise training may also be involved in the regulation of vitamin D through increasing VDR expression in skeletal muscle tissue and serum 25(OH)D levels [23, 24, 41]. Meanwhile, vitamin D supplementation can directly upregulate AMPK-GLUT-4 signaling pathway through VDR to increase glucose utilization and participate in exercise pathway of glucose utilization [42]. Therefore, the combined intervention of vitamin D and exercise on IR for T2DM patients in this study is scientific and novel, and findings of their combined effect from activating different ways of glucose utilization are expected to benefit both T2DM and other chronic metabolic diseases. Finally, we plan to further investigate protein expression related with glucose uptake in skeletal muscle tissue to elucidate the mechanism of the combined effect on IR in mice in our future study.

China is currently facing a growing threat from NCDs, and it shows no sign of abating. Prevention of NCDs including diabetes through promoting healthy eating and lifestyle has been elevated to a national public policy priority [2, 43]. In October 2016, the State issued the “Healthy China 2030” bringing the NCD issue into sharper and more concrete focus [44]. The findings from this study of vitamin D supplementation on IR for Chinese T2DM patients can also contribute to the alleviation of T2DM epidemic worldwide.

## Trial status

Active protocol version number: 1.3; January 1, 2019. The details of the protocol versions with the date of the amendment are provided in Table 3. Recruitment began on April 1, 2018. Currently, recruitment is ongoing and is expected to be completed in December 2020, and intervention and the last follow-up are expected to be completed in December 2021.

**Table 3 Tab3:** Protocol versions

Version	Date and changes
1.0	March 7, 2017, original protocol
1.1	March 1, 2018, introduction and background was improved
1.2	July 15, 2018, amendments of the inclusion and exclusion criteria
1.3	January 1, 2019, more comprehensive plan of the analysis was incorporated

## Data Availability

Not applicable.

## Abbreviations

ABI: Ankle-brachial index
ANOVA: Analysis of variance
AMPK: AMP-activated protein kinase
CG: Control group
DXA: Dual-energy X-ray absorptiometry
EG: Endurance exercise group
GLUT-4: Glucose transportor-4
HbA1c: Glycated hemoglobin
HOMA: Homeostatic model assessment
IR: Insulin resistance
MHR: Maximal heart rate
OGTT: Oral glucose tolerance test
T2DM: Type 2 diabetes mellitus
VD: Vitamin D
VEG: Vitamin D and endurance exercise group
25(OH)D: 25-Hydroxyvitamin D
